**Table 3 Study groups and epochs foreseen in the study**

| Study groups         | Number of subjects      | Age (Min/Max) | Epochs          |                   |                 |                 |
|----------------------|-------------------------|---------------|-----------------|-------------------|-----------------|-----------------|
|                      |                         |               | Screening epoch | Vaccination epoch | Challenge epoch | Follow-up epoch |
| RRR                  | 84                      | 18 - 50 years | x               | x                 | x               | x               |
| ARR                  | 84                      | 18 - 50 years | x               | x                 | x               | x               |
| Infectivity controls | 4 - 6 per challenge day | 18 - 50 years | x               |                   | x               | x               |

ARR = first dose with Ad35.CS.01, second and third doses with RTS,S/AS01B

RRR = three doses of RTS,S/AS01B

- Control: active control. The group receiving three doses of RTS,S/AS01B will be the comparator group. In addition, there will be infectivity controls for the challenge epoch (i.e. volunteers who will not receive any immunization but will be subjected to the sporozoite challenge).
- Vaccination schedule: 0-1-2 months followed by a challenge 21 days (3 weeks)  $\pm$  7 days after the third vaccination.
- Safety considerations:

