#### **5.4.3. Malaria Challenge**

Volunteers from both study groups completing their immunization course will be challenged with sporozoite-infected mosquitoes to determine whether the expected protective response has developed. Such challenges are mandated by the absence of any laboratory tests that will unequivocally predict protection. The challenge is scheduled to occur approximately 21 days (3 weeks) after the last vaccination visit (Study Day 77) and will be performed in a staggered fashion. The first 56 eligible subjects (28 subjects per study group) will be enrolled and vaccinated (Cohort A). Among the 56 vaccinated individuals a random selection of subjects eligible for challenge will be done according to the local SOP to ensure that a maximum of 46 vaccinated individuals (balanced by group) will progress to the challenge phase. The remaining subjects will not be challenged but will be followed for safety and immunogenicity up to 6 months after the last vaccination.

Unimmunized infectivity control volunteers will also be challenged to verify the adequacy of the challenge. The use of 4 to 6 unimmunized, malaria-naïve controls per challenge day is adequate since the procedure described has generally successfully infected such volunteers [Gordon, 1995]. The challenge of vaccinated subjects from Cohort A will be done at the WRAIR Insectary.

After safety and efficacy assessment for Cohort A, subjects from Cohort B and C (approximately 56 subjects per cohort) will be vaccinated. Of these subjects, a maximum of 46 vaccinated study participants per cohort will progress to the challenge phase. The challenge of Cohorts B and C will be conducted in parallel at WRAIR Insectary and the University of Maryland, CVD, respectively. Malaria-infected mosquitoes for challenge at the University of Maryland will be transported by WRAIR investigators to the insectaries at the University of Maryland for challenge of human subjects.

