#### **5.4.3.3. Infection of Human Volunteers**

Mosquitoes infected approximately 2-3 weeks earlier that are likely to contain sporozoites in their salivary glands will be allowed to feed on the volunteers. For each volunteer, five mosquitoes will be allowed to feed over five minutes, after which they will be dissected to confirm how many were infected, and the salivary glands scored. If required, additional mosquitoes will be allowed to feed until a total of five infected mosquitoes with a minimum 2+ salivary gland score have fed [Wirtz, 1987]. The mosquito feedings will be performed in the secure insectary of the Department of Entomology at WRAIR for two study cohorts and at the University of Maryland, CVD for the third study cohort. Volunteers will be observed for 30 minutes following completion of the sporozoite challenge in order to assess them for any evidence of acute allergic reactions related to mosquito exposure. To date, no severe allergic reactions related to mosquito bites have been documented in the context of the WRAIR malaria challenge model. Routinely, transient local allergic reactions (itching, rash) typical of mosquito bites occur at sites of the bites.

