**Table 11 Intervals between study visits for vaccinees**

| Interval                                  | Optimal length of interval  | Maximum interval allowed  |
|-------------------------------------------|-----------------------------------------|---------------------------------------|
| Visit 1 → Visit 3 (1 st vac)   | 0 to 90 days                            | 90 days                               |
| Visit 3 → Visit 7                         | 6 days                                  | +/- 1 days                            |
| Visit 3 → Visit 8                         | 14 days                                 | +/- 2 days                            |
| Visit 3 → Visit 9 (2 nd vacc)  | 28 days                                 | +/- 4 days                            |
| Visit 9 → Visit 13                        | 6 days                                  | +/- 1 days                            |
| Visit 9 → Visit 14                        | 14 days                                 | +/- 2 days                            |
| Visit 9 → Visit 15 (3 rd vacc) | 28 days                                 | +/- 4 days                            |
| Visit 15 → Visit 19                       | 6 days                                  | +/- 1 days                            |
| Visit 15 → Visit 20 (challenge)           | 21 days                                 | +/- 7 days                            |
| Visit 20 → Visit 40                       | 28 days                                 | +/- 2 days                            |
| Visit 40 → Visit 41                       | 35 days                                 | +/- 7 days                            |
| Visit 41 → Visit 42                       | 96 days                                 | +/- 7 days                            |

 Whenever possible the investigator should arrange study visits within this interval

 Subjects will not be eligible for inclusion in the cohort for ATP analysis of immunogenicity and efficacy if they make the study visit outside this interval

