### 6.3. Dosage and administration of study vaccines

**Table 22 Dosage and administration**

| Type of contact and timepoint | Dose | Treatment Group | Vaccine                 | Route  | Site  | Side  |
|-------------------------------|------|-----------------|-------------------------|--------------------|-------------------|-------------------|
| visit 3 (Day 0)               | 1    | ARR             | Ad35.CS.01              | IM                 | D                 | N-D               |
|                               | 1    | RRR             | RTS,S/AS01 B | IM                 | D                 | N-D               |
| visit 9 (Day 28)              | 2    | ARR , RRR       | RTS,S/AS01 B | IM                 | D                 | N-D               |
| visit 15 (Day 56)             | 3    | ARR , RRR       | RTS,S/AS01 B | IM                 | D                 | N-D               |

Intramuscular (IM)

Deltoid (D)

Non-dominant (N-D) except for variances like tattoos, rashes, burns or other skin disorders subject to the discretion of the investigator.

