**Table 26 Reporting periods for adverse events, serious adverse events and pregnancies**

| Study activity                                                                                              | Pre-V1    | V1 | 6 days post-V1 | 27 days post-V1 | V2 | 6 days post V2 | 27 days post-V2 | V3 | 6 days post V3 | Challenge | 29 days post-V3 | 29 days post-challenge | Study Conclusion |
|-------------------------------------------------------------------------------------------------------------|-----------|----|----------------|-----------------|----|----------------|-----------------|----|----------------|-----------|-----------------|------------------------|------------------|
| Study day                                                                                                   | -90 to -1 | 0  | 6              | 27              | 28 | 34             | 55              | 56 | 62             | 77        | 85              | 107                    | 236              |
| Reporting of solicited local and general AEs                                                                |           |    |                |                 |    |                |                 |    |                |           |                 |                        |                  |
| Reporting of unsolicited AEs                                                                                |           |    |                |                 |    |                |                 |    |                |           |                 |                        |                  |
| Reporting of SAEs                                                                                           |           |    |                |                 |    |                |                 |    |                |           |                 |                        |                  |
| Reporting of SAEs related to study participation or GSK concurrent medication/vaccination and any fatal SAE |           |    |                |                 |    |                |                 |    |                |           |                 |                        |                  |
| Reporting of pregnancies                                                                                    |           |    |                |                 |    |                |                 |    |                |           |                 |                        |                  |

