#### ***Primary safety endpoints***

- Occurrence of each solicited adverse event within 7-day follow-up period (day of vaccination and 6 subsequent days) after each vaccination.
- Occurrence of unsolicited adverse events within 30 days (day of vaccination and 29 subsequent days) after each vaccination, according to the Medical Dictionary for Regulatory Activities (MedDRA) classification.
- Occurrence of unsolicited adverse events within 30 days (day of challenge and 29 subsequent days) after challenge, according to the Medical Dictionary for Regulatory Activities (MedDRA) classification.
- Occurrence of serious adverse events (SAEs) within 30 days (day of vaccination and 29 subsequent days) after each vaccination, according to the Medical Dictionary for Regulatory Activities (MedDRA) classification.
- Occurrence of SAEs during the whole study period (from dose 1 up to study conclusion), according to the Medical Dictionary for Regulatory Activities (MedDRA) classification.

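### The 30-day safety windows after dose 3 always contain the malaria challenge, so challenge events are counted as post-vaccination events in primary safety endpoints

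*Protocol*

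**What the plan says.** Section 10.1 lists among the primary safety endpoints "Occurrence of unsolicited adverse events within 30 days (day of vaccination and 29 subsequent days) after each vaccination". It sets the same 30-day window for SAEs after each dose, and adds a separate endpoint, "Occurrence of unsolicited adverse events within 30 days (day of challenge and 29 subsequent days) after challenge". Section 10.8.4 tabulates unsolicited AEs over Day 0 to Day 29 after vaccination and does not cut the window at challenge.

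On timing, Table 22 places dose 3 at "visit 15 (Day 56"). Section 3 gives the schedule as "0-1-2 months followed by a challenge 21 days (3 weeks"), with 7 days' tolerance either way. Section 5.4.3 states: "The challenge is scheduled to occur approximately 21 days (3 weeks) after the last vaccination visit (Study Day 77"). In Table 11 the row "Visit 15 → Visit 20 (challenge") allows the same 21 days, plus or minus 7.

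On what is recorded, Section 8.3.1 collects every AE from the first dose to 30 days after challenge, whatever its cause. The glossary treats a solicited symptom that starts outside the solicited period as unsolicited. Section 5.4.3.3 says that, routinely, "transient local allergic reactions (itching, rash) typical of mosquito bites occur at sites of the bites".

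Table 26 has a column headed "27 days post-V1" and a matching one after the second dose. The column for 29 days after the third dose is at Study Day 85, to the right of the challenge column at Day 77.

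**The concern.** A post-vaccination endpoint should describe what follows vaccination. Here the last part of the dose 3 window also follows exposure to infected mosquitoes. For challenged subjects, bite reactions, fever or headache starting after challenge meet the definition of an unsolicited AE within 30 days of dose 3, and also meet the post-challenge definition.

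Two effects are possible, and they differ in kind. Events that challenge causes equally in both arms raise both rates and shrink any contrast between the regimens. Events caused by malaria depend on the efficacy outcome, so they could make the better-protected arm look safer after vaccination.

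A lesser question is whether the 30-day windows after doses 1 and 2 fit doses given 28 days apart.

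**Working it through.** **Inputs from the protocol.** Doses on Days 0, 28 and 56 (Table 22). Challenge 21 ± 7 days after dose 3 (Table 11). Window of the dose day plus 29 days (Section 10.1). 69 of 84 per group challenged (Section 4.1). Attack rate 50% in RRR, and 25% in ARR at the planned 50% relative reduction (Section 10.4). Usual pre-patent period 9 to 12 days, with 7 to 18 days seen in controls (Section 5.4.3.5).

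**Table 26's own figure.** End of the dose 3 window = 56 + 29 = Day 85, which reproduces.

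**Overlap with challenge** = 85 − challenge day + 1.
- Day 77 (nominal): 9 days, challenge days 0 to 8.
- Day 70 (earliest): 16 days, challenge days 0 to 15.
- Day 84 (latest): 2 days, challenge days 0 and 1.

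No permitted challenge day falls outside the window.

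**Dilution by events common to both arms (illustration).** Take true rates of 5% and 20%, the fourfold case in Table 30. That table's column is labelled for SAEs; the rates are borrowed only for scale. Suppose a share r of challenged subjects report a bite reaction (assumption). With q = (69/84) × r, each rate becomes 1 − (1 − rate) × (1 − q).
- r = 25%: q = 0.205; 24.5% against 36.4%, ratio about 1.5.
- r = 50%: q = 0.411; 44.0% against 52.9%, ratio about 1.2.
- r = 75%: q = 0.616; 63.5% against 69.3%, ratio about 1.1.

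**Malaria part, which can differ by arm.** The spurious RRR minus ARR difference in the share with any AE after dose 3 is

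(1 − b) × (69/84) × (0.50 − 0.25) × w × s,

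where b is the AE rate without malaria, w the share of infections patent inside the window, and s the chance that an infection yields an AE. All three are assumptions: b 30 to 90%, s 50 to 100%.

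For w, normal pre-patent periods with (mean, SD) of (10.5, 1.5), (10.5, 2), (11, 2) and (12, 2.5) days give 9.1%, 15.9%, 10.6% and 8.1% by challenge day 8, and 92 to 100% by day 15. The ranges used are 2 to 16% nominally and 90 to 100% for Day 70. The lower nominal end allows for the prolonged pre-patent period that Section 5.4.3.5 says incomplete protection may bring.
- Nominal, largest: 0.7 × 0.821 × 0.25 × 0.16 × 1 = 2.3 points. Smallest: 0.1 × 0.821 × 0.25 × 0.02 × 0.5 = 0.02 points.
- Everyone on Day 70, largest: 0.7 × 0.821 × 0.25 × 1 × 1 = 14.4 points. Smallest: 0.1 × 0.821 × 0.25 × 0.9 × 0.5 = 0.9 points.
- Everyone on Day 84: about 0.

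**Doses 1 and 2.** The Day 0 to 29 window after dose 1 includes Days 28 and 29, the day of dose 2 and the day after. The same holds for dose 2 and dose 3. Table 26 has columns at 27 days (Days 27 and 55), the day before the next dose.

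**The case against.** The strongest case is that the overlap is real but does little harm. Bite reactions strike both arms alike, because Section 3 balances the challenged subjects by group. On the planned schedule the window closes on challenge day 8, before the usual pre-patent period begins, and Section 5.4.3.5 notes that infection is in many cases found and treated before symptoms. Section 10.8.4 also provides MedDRA coding and a separate table of vaccine-related unsolicited AEs. It gives exact confidence intervals and specifies no between-arm safety test. The unsolicited-event holding rules in Section 5.4.4.1.3 require relatedness to vaccination. An event shown under two separately reported endpoints is not in itself an error.

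Most of this stands, and it limits the size of the problem. It does not correct the endpoint, which counts all unsolicited AEs. Relatedness is a judgement on individual events, and fever or headache may follow either exposure. Section 10.4 also frames safety as a fold increase in AE rates between arms, and that contrast is what common events dilute.

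A reader might infer that the post-vaccination rate is mostly a challenge effect, or that the better-protected arm gains about 20 points: 0.8 to 0.9 × (50 − 25) = 20 to 22.5. The documents support neither. The second figure puts everyone on Day 70, treats all vaccinees as challenged, lets every infection produce an AE and allows no other AE. The factor 69/84 alone reduces it to 16.4 to 18.5 points.

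A reader might also see a firm contradiction with Table 26, or acute reactions to dose 2 being charged to Ad35.CS.01. The body cells of Table 26 are empty in the text available, so its columns at 27 days may only mark the day before the next dose. The main acute reactions after dose 2 (pain, redness, swelling, fever, fatigue, headache, gastrointestinal symptoms, chills) are solicited AEs through Day 6 and do not enter this endpoint.

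**Conclusion.** The point holds as an endpoint-definition problem of moderate size. The overlap of 2 to 16 days, 9 nominally, is certain on the protocol's own dates. It affects both the unsolicited AE and the 30-day SAE windows after dose 3, although routine bite reactions bear on the former. It raises the post-dose-3 rate in both arms and dilutes any difference between regimens, by an amount that depends on how many bite reactions are reported, which the protocol does not state.

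A bias towards the better-protected arm can come only from malaria. It is about 0 to 2.3 percentage points on the nominal schedule. It becomes material, at about 1 to 14 points, only if everyone is challenged on Day 70. These ranges rest on the assumed background AE rate, pre-patent timing and symptom probability, and on the planned attack rates.

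The windows after doses 1 and 2 are a lesser matter: Section 10.1 and Table 26 should be reconciled.

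**What to change.** In Sections 10.1 and 10.8.4, for both the unsolicited AE and the 30-day SAE endpoints, end each post-vaccination window at the earliest of:
- Day 29 after the dose;
- the day before the next dose;
- the day before challenge.

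Count unsolicited AEs from challenge onward under the existing post-challenge endpoint; SAEs also remain in the whole-study SAE endpoint. Report exposure days by group, and align Table 26. The uncut Day 0 to 29 table can be kept as supplementary.

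No new data are needed and none are lost, because Section 8.3.1 already records AEs continuously. The cost is a shorter dose 3 window in challenged subjects: Days 56 to 76, or 21 days, nominally, and 14 to 28 days over the permitted challenge dates. Unchallenged subjects keep 30 days, which is why exposure must be shown. Late vaccine events in challenged subjects would leave the main post-vaccination table and appear only among post-challenge events, so the supplementary table is worth keeping.

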### **10.2. Secondary endpoints**

#### ***Secondary efficacy endpoint***

- Time to *P. falciparum* parasitemia, defined by a positive blood slide, following sporozoite challenge.

#### ***Secondary immunogenicity endpoints***

- Anti-CS (RT) and anti-HBs antibody titres at specified time points.
- Anti-Ad35 neutralizing antibody titers at specified time points.
- Frequency of CS (total CS or RT)-specific, HBs-specific T cells at specified time points.

### 10.3. Exploratory endpoints

#### *Exploratory efficacy endpoints*

- Occurrence of *P. falciparum* parasitemia, defined by a positive PCR, following sporozoite challenge.
- Time to *P. falciparum* parasitemia, defined by a positive PCR, following sporozoite challenge.

#### *Exploratory immunogenicity endpoints*

- Frequency of Ad35-specific T cells at specified time points.
- Antibody titres against full-length CS and CS specific peptides other than repeat.
- Isotype, affinity and functionality of CS-specific antibodies.
- Multivariant analysis (systems biology approach) using high-throughput technologies such as gene expression profiling, multiplex analysis of cytokines and chemokines (Luminex), and multiparameter flow cytometry for plasmablast analysis and B cell ELISPOT.

### 10.4. Estimated sample size

For the final analysis, the target enrollment for this study will be 168 volunteers to ensure 69 subjects per study groups will undergo sporozoite challenge, given an approximate 20% estimated drop-out rate, based on past experience.

For the primary endpoint, the study will have 82% power to demonstrate an increase of 50% efficacy (2-sided Fisher exact test,  $\alpha=5\%$ ) of the ARR group over the RRR group, assuming a 50% attack rate in the RRR group. The increase in VE of the ARR group over the RRR alone group is defined as  $100 \times (1 - \text{AR}_{\text{Ad35.CS}} / \text{AR}_{\text{RTS,S}})$  where AR is the attack rate in the 2 groups.

The trial will have 80% power (2-sided Fisher exact test,  $\alpha=5\%$ ) to detect the following fold increase in AE rates of the ARR group over the RRR group (right column), depending on the rate of AEs in the RRR group (left column) (see [Table 30](#)).

**Table 30 Percentages with 80 percent power to detect event rate fold increase in the ARR group**

| SAEs rates in RRR group | 80% power to detect event rate fold increase in ARR group |
|-------------------------|-----------------------------------------------------------|
| 1%                      | 12                                                        |
| 5%                      | 4                                                         |

ARR group = first dose with Ad35.CS.01, second and third doses with RTS,S/AS01B

RRR group = three doses of RTS,S/AS01B

## **10.5. Study cohorts to be evaluated**

### **10.5.1. Total vaccinated cohort**

The Total vaccinated cohort for analysis of safety will include all subjects with at least one vaccine administration documented. The Total vaccinated cohort analysis will be performed per treatment actually administered.

### **10.5.2. According-to-protocol (ATP) cohort for analysis of efficacy**

The ATP cohort for analysis of efficacy will include all subjects included in the Total vaccinated cohort who received all vaccinations according to protocol procedures within the protocol specified intervals, underwent challenge and for whom data concerning efficacy endpoint measures are available.

